**Discussion:**

The aim of this study is to evaluate the efficacy and safety of acupuncture paired with herbal medicine for the treatment of patients with prediabetes.

**Trial registration:**

Chinese clinical trials register ChiCTR-INR-16008891. Registered on 23 July 2016.

**Electronic supplementary material:**

The online version of this article (doi:10.1186/s13063-017-2014-4) contains supplementary material, which is available to authorized users.

## Background

Since the American Diabetes Association (ADA) integrated glycosylated hemoglobin (HbA_1c_) level into the diagnostic criteria of diabetes mellitus in its 2010 guidelines [1] and included it as a criterion for the diagnosis of prediabetes, the morbidity of prediabetes has significantly increased. A large epidemiological investigation of diabetes mellitus in China in 2013 [2] noted that among the Chinese adult population (aged 18 years and above), the overall prevalence rates of diabetes mellitus and prediabetes were estimated to be as high as 11.6% and 50.1%, respectively, suggesting that diabetes mellitus has become a major public health problem in China. Diabetes mellitus can damage the heart, blood vessels, eyes, kidneys, and nervous system, leading to complications throughout the body, including myocardial infarction, stroke, kidney failure, leg amputation, visual loss and nerve damage; furthermore, diabetes can increase the overall risk of disability and premature death [3]. Therefore, it is imperative to prevent and treat this condition.

Long-term follow-up data from the UK and the USA [4–6] showed that approximately 5−11% of patients with prediabetes ultimately progressed to diabetes mellitus every year. Data from China [7] has shown that the incidence of diabetes mellitus among patients with IGT is 24.3% every 2 years. According to the ADA expert panel, up to 70% of individuals with prediabetes will eventually develop diabetes mellitus [8]. In a Chinese diabetes mellitus prevention trial that lasted for 20 years, the 20-year cumulative incidence of diabetes mellitus was more than 90% [9].

Several trials have demonstrated significant reductions in the risk of developing diabetes mellitus among individuals with prediabetes after lifestyle or drug-based interventions [8]. The earlier that prediabetes can be addressed, the lower the risk of developing diabetes mellitus. Therefore, actively screening and treating prediabetes has been widely considered a topic of importance in the prevention of diabetes mellitus. In China, traditional Chinese medicine (TCM) including acupuncture and herbal medicine is an effective method for treating diabetes mellitus. The concept of “preventing disease before it starts or is diagnosed” in TCM theory is very suitable for intervening with prediabetes to prevent diabetes mellitus. The Chinese Medical Doctor Association recently launched a nationwide screening for diabetes mellitus and prediabetes. Based on this investigation, our trial focuses on the efficacy and safety of TCM for the treatment of patients with prediabetes.

### Progress of prediabetes

It is currently generally accepted that the most effective treatment for prediabetes is lifestyle intervention. The main risk factors for type-2 diabetes include genetics, ethnicity, age, overweight or obesity, unhealthy diet, insufficient physical activity, and smoking. Other than genetics, ethnicity and age, all of the other factors can be modified through behavioural and environmental changes. A 20-year follow-up study in China, *Da Qing* (China *Da Qing* Diabetes Prevention Study (CDQDPS)) [9], showed that compared with control participants who did not receive an intervention, IGT patients who underwent an active lifestyle intervention for 6 years had a 43% lower incidence of diabetes mellitus and a 13% lower 20-year cumulative incidence over the 20-year period. According to the well-known American Diabetes Prevention Program (DPP) [10], which included 3234 fasting plasma glucose (FPG) patients and had an average follow-up of 2.8 years, the incidence of diabetes mellitus development each year in participants in the placebo, metformin and lifestyle groups was 11.0%, 7.8%, and 4.8%, respectively. The DPP also showed that a lifestyle intervention was more effective than metformin. A systematic review and meta-analysis of different intervention strategies for preventing type-2 diabetes [11] revealed that several pharmacological interventions (for example, antidiabetic drugs, cardiovascular drugs, and lipid-affecting drugs) also prevented or delayed type-2 diabetes mellitus; however, in the majority of studies, pharmacological interventions were not as effective as changing diet and physical activity, and the effects dissipated after the medication was discontinued. The Global Report on Diabetes, published by the World Health Organization (WHO) in 2016 [3], suggested that diet and physical activity interventions are more effective than medication for preventing diabetes mellitus. As there is a lack of sufficient evidence showing that pharmacological interventions have long-term efficacy and health economic benefits for patient with prediabetes, the latest guidelines for the intervention and treatment of type-2 diabetes released in 2013 by the Chinese Diabetes Society [12] did not recommend using pharmacological interventions to prevent diabetes mellitus. Therefore, it is accepted worldwide that the most effective method of preventing diabetes mellitus is lifestyle intervention based on health education.

### Prevention and treatment of prediabetes with TCM

TCM has long been used by Chinese doctors to treat the symptoms of diabetes mellitus. “Consumptive thirst,” the main symptom of early diabetes, has been described in the TCM classic the “*Yellow Emperor’s Inner Canon*.” However, the long duration of TCM application does not mean that it is always effective and scientific. It is necessary to study the effects of TCM in randomized controlled trials (RCTs). Of all the clinical trials for “diabetes mellitus” registered in the Chinese Clinical Trial Registry (http://www.chictr.org.cn/index.aspx) before 11 August 2016, 50 mentioned TCM methods (including Chinese medicine decoctions, tablets or capsules, active ingredients of herbal medicine, acupuncture, massage or *tuina*, and traditional exercises) as an intervention for diabetes mellitus, and five targeted prediabetes. Of these, only four trials had published related papers on MEDLINE (study protocols for three trials [13–15] and results for one trial [16, 17]). We look forward to reviewing further research articles on the effects of TCM on prediabetes or diabetes mellitus with RCT protocols that scientifically and objectively assess the role of TCM in treating prediabetes or diabetes mellitus.

### Individualized treatment based on syndrome differentiation

TCM is a unique medical system that is independent of modern medicine and uses a thoroughly different mode of thinking to guide the diagnosis and treatment of diseases; this mode is difficult to explain using modern medical theories. There are numerous complex components in only one herb, and this leads to a specific herb having many pharmacological treatment targets; consequently, it is difficult to fully reveal the mechanisms of an herb through traditional laboratory methods. As TCM is characterized by individualized treatment based on syndrome differentiation, it is also subject to the shortcoming of poor repeatability of treatment efficacy. As a result, many people, including scientists, still consider TCM to be “pseudoscience” and doubt its true effects. Elucidating the role of TCM in a way that is understandable by modern medicine, and optimizing TCM treatments using provable methods, are goals continually pursued by many TCM researchers.

The greatest advantage of TCM treatment is the ability to individualize treatment based on syndrome differentiation, as therapeutic prescriptions can be adjusted according to minute changes in organ function to ensure each time that the prescription is the most appropriate option for the specific condition of the patient. Therefore, using an unchanging prescription in clinical trials cannot completely reveal the effects of TCM.

In this clinical trial, we intend to treat prediabetes using a basic herbal medicine formula with components and doses that are adjusted according to the changes in patient’s symptoms. The herbal medicine formula will be paired with an acupuncture acupoint prescription to observe the maximum effects of TCM on prediabetes. Moreover, objective laboratory examinations that reflect blood glucose level will be performed and will provide the primary outcomes, demonstrating the precise hypoglycaemic effects of TCM.

### Herbal medicine formula and acupuncture acupoint prescription

The basic herbal medicine formula in this trial consists of *Radix Astragali* 30 g, *Radix Codonopsis* 15 g, *Rhizoma Atractylodis Macrocephalae* 15 g, round cardamom fruit 15 g, *Dendrobium Herba Dendrobii* 20 g, *Rhizoma Dioscoreae* 20 g, *Radix Angelicae Sinensis* 20 g, white paeony root (*Radix Paeoniae Alba*) 20 g, barbary wolfberry fruit (*Fructus Lycii*) 15 g, Poria 20 g, *Semen Coicis* 20 g, flower of the white hyacinth bean/*Semen Lablab Album* 15 g, three pieces of Ginger *Rhizoma Zingiberis*, and three *Fructus Jujubae. Radix Astragali* is the main herb in many ready-made Chinese medicines for diabetes mellitus, such as the *JinQi-Jiangtang* tablet [15, 18], and its effective components are considered to be beneficial for diabetes mellitus [19–21]. Both in vitro and in vivo experiments [22, 23] have shown that SR10, an herbal formulation consisting of the aqueous extracts of *Radix Astragali*, *Radix Codonopsis*, and barbary wolfberry fruit (*Fructus Lycii*), appears to reduce the apoptosis of streptozotocin-treated pancreatic β-cells and decrease blood glucose levels in a mouse model of type-2 diabetes mellitus through its antioxidative effects. *Danggui Buxue Tang*, a simple combination of *Radix Astragali* and *Radix Angelicae Sinensis* (5:1), is suggested to be a novel therapeutic approach for the prevention and treatment of diabetic nephropathy in rats with streptozotocin-induced diabetes mellitus [24]. Furthermore, a natural product called dehydrotrametenolic acid isolated from Poria was shown to act as an insulin sensitizer that could induce adipose conversion in vitro and reduce hyperglycaemia in mouse models of noninsulin-dependent diabetes mellitus [25]. *Rhizoma Dioscoreae* and Poria are two types of herbs in the TCM formula *LiuWeiDiHuangWan*, which has been shown to be effective in diabetes mellitus and its complications, and the mechanisms of action have been discussed [26–28]. Some spices, including Ginger (*Rhizoma Zingiberis*), have been reported to have hypoglycaemic effects [29]. Ginger (*Rhizoma Zingiberis*) shows antidiabetic therapeutic effects by increasing insulin sensitivity/synthesis/release, protecting β-cells of the pancreatic islets, improving carbohydrate and lipid metabolism, reducing fat accumulation, decreasing oxidative stress, increasing glucose uptake by tissue, and inhibiting enzymes linked to diabetes mellitus and inflammation [30–33]. Additionally, *Fructus Jujubae*, which is considered food, is also found to have a protective role against diabetes-induced biochemical and histopathological abnormalities by maintaining serum insulin levels, increasing antioxidant capacity, and reducing concentrations of blood lipids and C-reactive protein [34]. The relationship between diabetes mellitus and the other herbs included, such as *Rhizoma Atractylodis Macrocephala*e, round cardamom fruit, *Dendrobium Herba Dendrobii*, white paeony root (*Radix Paeoniae Alba*), *Semen Coicis*, and flower of the white hyacinth bean/*Semen Lablab Album*, have not been studied pharmacologically; however, they are often used in clinical practice to treat diabetes mellitus.

For the acupuncture intervention for prediabetes, we chose [name] “*Tongyuan* needling technique” which was developed to treat chronic diseases by regulating the body’s primordial and visceral *qi* [35]. The principal acupoints include *Pishu* (BL20), *Weishu* (BL21), *Ganshu* (BL18), *Zhangmen* (LR13), *Zhongwan* (RN12), *Qimen* (LA14), and *Zhiyang* (DU9), with supplementary acupoints of *Taichong* (LR3), *Hegu* (L14), *Zusanli* (ST36), *Yinlingquan* (SP9), *Sanyinjiao* (SP6), *Fenglong* (ST40), *Shangjuxu* (ST37), and *Xiajuxu* (ST39). Several studies have obtained some positive findings in treating diabetes mellitus with acupuncture [36]. The specific acupoint that has been studied the most is *Zusanli* (ST36). It has been found that performing acupuncture at *Zusanli* (ST36) can have a hypoglycaemic effect in fasted rats with type-2 diabetes mellitus and also in obese women with a restricted caloric diet [37] and can also decrease the expression of neuropeptide Y (NPY) which is known to increase appetite by acting on the hypothalamus [38] and nitric oxide synthase in the periaqueductal gray matter area [39] of rats with streptozotocin-induced diabetes.

## Methods/design

### Objectives

To evaluate the effectiveness (both long-term and short-term) and safety of acupuncture paired with herbal medicine for prediabetes compared with health education.

### Research type

Randomized controlled trial (RCT).

### Screening of participants

Eighty prediabetes patients will be divided into the treatment group and the control group (1:1). Participants will be enrolled according to the diagnosis and inclusion criteria (please refer to the next section).

### Groups

Treatment group: acupuncture and herbal medicine intervention combined with lifestyle interventionControl group: lifestyle intervention only

### Interventions

#### Arrangement for intervention

All researchers in this study will be trained prior to participation. Participants will be instructed by trained researchers on how to use their medication and their involvement in the study.

#### Lifestyle intervention

A series of six lectures on healthy lifestyles for prediabetes will be provided to participants by researchers once every 4 weeks. The first lecture will occur when the participants are included in the study. The researchers will develop an individualized diet and exercise program for each participant, including a reasonable balance of calories, proteins and carbohydrates, a low-salt and low-sugar diet, and the type and amount of daily exercise, and will advise them to stop practicing certain poor dietary habits. Risk factors, such as smoking and alcohol consumption, will be strictly controlled. A diary to document lifestyle habits will be delivered to every participant, requiring them to record their daily diet intake and exercise, and diary entries will be checked by researchers every 4 weeks.

#### Acupuncture intervention

All participants in the treatment group will visit the researchers once every 8 days and be treated with acupuncture. The acupoint selection for acupuncture will be as follows: the principal acupoints include *Pishu* (BL20), *Weishu* (BL21), *Ganshu* (BL18), *Zhangmen* (LR13), *Zhongwan* (RN12), *Qimen* (LA14), and *Zhiyang* (DU9), and the supplementary acupoints will be *Taichong* (LR3), *Hegu* (L14), *Zusanli* (ST36), *Yinlingquan* (SP9), *Sanyinjiao* (SP6), *Fenglong* (ST40), *Shangjuxu* (ST37), and *Xiajuxu* (ST39). All acupoints will be stimulated by neutral reinforcement and reduction of movement, and the needles will be left in the acupoints for 30 min before withdrawal. The acupuncture intervention will last 24 weeks, during which each participant will receive 21 treatment sessions.

#### Herbal medicine intervention

All participants in the treatment group will visit the researchers once every 8 days, when the same Chinese doctor will examine them using four TCM diagnostic methods including inspection, listening and smelling, inquiry, and pulse-taking and palpation. The basic herbal medicine formula in this trial consists of *Radix Astragali* 30 g, *Radix Codonopsis* 15 g, *Rhizoma Atractylodis Macrocephalae* 15 g, round cardamom fruit 15 g, *Dendrobium Herba Dendrobii* 20 g, *Rhizoma Dioscoreae* 20 g, *Radix Angelicae Sinensis* 20 g, white paeony root *Radix Paeoniae Alba* 20 g, barbary wolfberry fruit *Fructus Lycii* 15 g, Poria 20 g, *Semen Coicis* 20 g, flower of the white hyacinth bean/*Semen Lablab Album* 15 g, three pieces of Ginger (*Rhizoma Zingiberis*), and three of *Fructus Jujubae*. The components and dose of the formula will be adjusted according to the changes in patient symptoms every 8 days by the same doctor. Participants will receive all herbs from the same hospital and will be instructed on how to make the decoction. Each decoction should be taken four times in 2 days, twice a day. The participants will be instructed to stop and rest for 2 days between two separate decoctions (i.e., take one decoction every 4 days). The herbal medicine intervention will last 24 weeks, during which each participant will receive 42 decoctions. Participants will be asked to record their changes in symptoms daily using a form reviewed by their doctor every 8 days.

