**Methods/design:**

An RCT will be implemented in this study, using a72-week study period (24 weeks for the intervention and 48 weeks for follow-up). Participants will be recruited from the Fifth Affiliated Hospital of Guangzhou Medical University in China. Eighty participants will be randomized to the treatment group (acupuncture plus herbal medicine and health education) or the control group (health education only), 40 participants in each. People included in this study must have been diagnosed with prediabetes using Western medicine criteria. The endpoint indices include the incidence of diabetes mellitus and the reversion rate. The primary outcome is fasting plasma glucose (FPG) level, 2-h plasma glucose (2-hPG) level after a 75-g oral glucose tolerance test (OGTT), and glycosylated hemoglobin (HbA_1c_) level. Secondary outcomes include the following: Body Mass Index (BMI); hemorheology, including shear rates of whole-blood viscosity and plasma viscosity. Safety indices include hepatic (ALT, AST) and renal function (BUN, Cr) and records of adverse events, including diarrhoea, colds, pharyngitis, and sleep disorders. Quality control will be implemented, including quality control of the laboratory, researchers, participants, investigational drugs, data and documents, occurrence of bias, supervision, among others, according to uniform standard operating procedures (SOPs) which have been established by the Good Clinical Practice (GCP) office of the Fifth Affiliated Hospital of Guangzhou Medical University.

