### Adverse event monitoring

#### Reporting of adverse events

Participants will be required to immediately report adverse events (AEs) to researchers when they occur. Researchers will also ensure that the study is proceeding as intended every 8 days when participants visit them at the hospital.

When serious adverse events (SAEs) occur, researchers must complete an SAE Form and immediately report the event to the project leader and the Ethics Committee of the Fifth Affiliated Hospital of Guangzhou Medical University. The event should also be reported to the China Food and Drug Administration (CFDA) within 24 h.

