#### Relationship between adverse events and changes in symptoms

This trial differs from other trials, as the formulas prescribed to the participants will be adjusted according to the changes in symptoms caused by receiving the last formula. Therefore, AEs can be useful to the Chinese doctor for adjusting the prescribed formulas.

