#### Measures for compliance of participants

Researchers should verify that the participants have received the herbal medicine in time and should explain how to make the correct decoction. Participants in both the treatment group and lifestyle group will be asked to visit the researchers every 8 days to receive acupuncture treatment and new herbal medicine or to receive only the examination by diagnostic methods. The lifestyle diary will be checked by researchers every 4 weeks. Therefore, participant compliance can be examined by the researchers.

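### The daily symptom form belongs to the herbal treatment only, so the adverse event records named as a safety index are gathered more intensively in one arm

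*Protocol article*

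**What the plan says.** **Treatment arm.** The Herbal medicine intervention section opens with the treated group: "All participants in the treatment group will visit the researchers once every 8 days, when the same Chinese doctor will examine them". It goes on to the formula and its revision: "The components and dose of the formula will be adjusted according to the changes in patient symptoms every 8 days by the same doctor". It closes with the symptom form: "Participants will be asked to record their changes in symptoms daily using a form reviewed by their doctor every 8 days".

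**Control arm.** Measures for compliance of participants brings both groups in every 8 days. Treated participants come for acupuncture and new herbs; the others come "or to receive only the examination by diagnostic methods". The diary that the Lifestyle intervention section gives to everyone covers diet and exercise, not symptoms, and is checked every 4 weeks.

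**Both arms.** Reporting of adverse events relies on the participant: "Participants will be required to immediately report adverse events (AEs) to researchers when they occur". It adds a general check: "Researchers will also ensure that the study is proceeding as intended every 8 days when participants visit them at the hospital". Documentation of adverse events requires an AE Report Form but does not link it to the symptom form.

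**Use of the records.** The abstract's safety indices include "records of adverse events, including diarrhoea, colds, pharyngitis, and sleep disorders". The section on adverse events and symptom changes concludes: "Therefore, AEs can be useful to the Chinese doctor for adjusting the prescribed formulas".

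**The concern.** The Objectives section asks about safety compared with health education. Colds, sore throats and poor sleep occur without any treatment, so their frequency under acupuncture and herbs means something only beside a control arm observed in the same way. A daily written prompt with regular review will usually pick up more mild complaints than an inquiry every 8 days plus self-report.

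Allocation is open to participants and to the treating doctor (Blinding; Allocation concealment), so nothing in the design evens this out. Laboratory safety tests are scheduled only at visits 1 and 25. Adverse event records are therefore the only safety information gathered during the 24 weeks between. Events never recorded in controls cannot be recovered at the analysis stage.

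**Working it through.** **1. Whom the form covers.** The sentence on the form says participants without restriction. Three features point to the treated arm: the section is about the herbal treatment, it opens with the treatment group, and the symptom record feeds a formula that controls do not take. Where the article describes a diary for both arms, it says so explicitly (Lifestyle intervention).

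**2. The two arms side by side, as described.**

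| | Treatment | Control |
|---|---|---|
| Daily symptom record | Yes | None described |
| Review of that record | Every 8 days | None described |
| Examination, including inquiry | Every 8 days | Every 8 days |
| Self-report of adverse events | Yes | Yes |
| Rule sending recorded symptoms to the AE Report Form | None stated | Not applicable |

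The difference is therefore form plus inquiry plus self-report against inquiry plus self-report.

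**3. Intensity.** 24 weeks × 7 = 168 days, so up to 168 daily records. 168 / 8 = 21 reviews, which matches the 21 sessions given under Acupuncture intervention.

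**4. Illustration of size.** All rates here are assumptions; the documents give none. Let p be the true share with a mild event, equal in both arms. Let 0.9 be the capture rate in the treatment arm and c the capture rate in controls. The recorded gap is p × (0.9 − c).

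| p | c = 0.9 | c = 0.7 | c = 0.5 |
|---|---|---|---|
| 0.2 | 0 | 18% v 14%: 4 points | 18% v 10%: 8 points |
| 0.3 | 0 | 27% v 21%: 6 points | 27% v 15%: 12 points |
| 0.4 | 0 | 36% v 28%: 8 points | 36% v 20%: 16 points |

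With p = 0.3 and c = 0.5, that is 0.27 × 40 = 10.8 against 0.15 × 40 = 6 participants, with no true difference. The column c = 0.9 is the case in which inquiry every 8 days does as well as the form.

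**5. Sign.** Suppose instead that only half of the treatment-arm captures reach the AE Report Form, since no rule requires the transfer. Then 0.27 × 0.5 = 13.5% stands against 15%, and the gap reverses.

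**6. What is not touched.** Safety indices lists only ALT, AST, BUN and creatinine. Criteria for the evaluation of safety judges safety on liver and kidney function, and the safety set is assessed on laboratory results. None of these depends on the form.

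**The case against.** **Controls are not left to spontaneous report.** A reader might infer that they are. The documents do not support that: the diagnostic methods used at the control visits include inquiry, so controls are asked about their condition every 8 days. The Discussion also speaks of participants generally when it says symptom changes are recorded by these methods and entered in the data system, although the purpose it gives is formula adjustment. This narrows the difference between the arms. It does not remove it, because an inquiry made for diagnosis is not a daily written record.

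**Adverse events are not declared to be symptoms.** A reader might infer that complaints in the treatment arm are to be relabelled. The Discussion can be read as saying only what drives the formula, and the adverse event sections require reporting with no exemption by arm. What stands is narrower: no stated rule says when an entry on the form becomes an adverse event.

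**The form may reach both arms.** The schedule figure and the additional files on visit contents and data capture are not shown and could settle this. That is a real limit on certainty, but the text as published points to one arm.

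**A shared form will not cure open-label reporting.** True. It removes the difference in instrument, not the difference in expectation.

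**No between-arm test of adverse events is planned.** Also true, so no false-positive rate is claimed here. The records remain a declared safety index and would still be read across arms.

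**Conclusion.** The point holds in a limited form. As described, the adverse event records named in the abstract would be gathered more intensively in the treatment arm of an open-label trial, with no stated route from the symptom form to the AE Report Form. An arm difference in mild events could then be a matter of ascertainment.

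The firm figures are up to 168 daily records and 21 reviews per treated participant, against none described per control. The percentage gaps are illustrations under assumed rates and establish neither direction nor size.

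It would go too far to conclude that the whole safety comparison with health education cannot be interpreted. The formal verdict rests on laboratory values, which the form does not affect. The point also rests on reading the form as part of the herbal treatment, which the section's placement and purpose support but its wording does not state outright.

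**What to change.** Move the daily symptom form from the herbal treatment section to the procedures common to both arms. Issue it to every participant from visit 1 to visit 25, and review it with the same questions at the 8-day visits already scheduled for both groups. State that any new or worsened symptom on the form is entered on the AE Report Form in both arms, whether or not it also informs the formula. If the additional files already provide for this, one sentence in the main text is enough.

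The cost is one existing form for 40 more participants and a few minutes at visits that already take place. The downsides are some added diary burden for controls and a higher recorded adverse event count. The article reports that the trial had not started at submission, so as of that date the change could have been made before any data were collected.
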